### Assessments

#### Radiographic assessments.

Initial periapical radiographs will be obtained to discard the possibility of pulp involvement. Follow-up radiographs will be taken in cases of pain symptoms that justify additional exposure.

#### Clinical assessment.

The clinical assessment will be performed by an examiner blinded to the allocation of the teeth to the different groups. The criteria will be the retention of the restorative material in the cavity, posteruptive breakdown of the enamel adjacent to the restoration and the occurrence of secondary caries. The criteria of the modified USPHS index will be used for the assessment. The restoration will be characterized as a failure and the tooth will be excluded from the study if the C score is determined for any of the USPHS criteria [27]. Photographs will be taken using a digital single-lens reflex (DSLR) camera (Canon EOS 700D; Canon, Tokyo, Honshu, Japan) to complement the clinical data. These photographs will be taken before and after the restorative treatment, as well as during all follow-up periods, following the same standardized parameters. This will ensure consistency in clinical data collection. The visual demonstration will contribute to any necessary clarifications and make the discussion and documentation of the cases more efficient [28].

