## Introduction

Molar-Incisor Hypomineralization (MIH) is a developmental enamel defect that impairs mineralization during the amelogenesis process, primarily affecting the first permanent molars and, in some cases, the incisors [1]. Molar-Incisor Hypomineralization (MIH) is characterized by well-defined, asymmetrical opacities with varying color shades. Darker opacities exhibit a higher susceptibility to fractures due to a greater compromise in their mineral composition [1]. MIH poses a significant clinical challenge due to dental hypersensitivity, an increased risk of caries, and difficulties in achieving adequate adhesion of restorative materials [2].

Hypersensitivity is a common symptom in patients with MIH and may occur in teeth with or without post-eruptive fractures. The severity of clinical manifestations is directly correlated with the intensity of hypersensitivity [3]. Although the underlying mechanisms of hypersensitivity in MIH-affected teeth are not yet fully elucidated, it is hypothesized that chronic stimuli contribute to a subclinical pulpal inflammation. This process is likely driven by bacterial infiltration through the porous enamel, leading to persistent nociceptive responses [4].

Photobiomodulation with low- or high-power laser is a potential treatment method for dentinal hypersensitivity [5]. Photobiomodulation (PBM) with low-level laser (LLL), such as GaAlAs or He-Ne, has no known side effects when administered with the appropriate settings. The mechanism of action is based on the induction of changes in nerve transmission to control pain. Nerve cells are stimulated and the sodium/potassium pump in the cell membrane increases the amplitude of the action potential, thus blocking the transmission of the pain stimulus. Moreover, PBM enhances cell regeneration capacity and reduces inflammation [6,7].

Teeth affected by Molar-Incisor Hypomineralization (MIH) exhibit a reduction in mineral content, accompanied by an increase in organic content due to the retention of proteins during the mineralization process. This structural modification compromises the adhesion of restorative materials to the hypomineralized enamel, making it one of the main factors associated with the failure of restorative procedures. As a result, there is a higher failure rate in treatments, often requiring re-treatments and restorative replacements over time. [8,9].

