### Objectives

Primary Objective: To determine whether photobiomodulation combined with a new photopolymerizable resin improves hypersensitivity in MIH-affected carious molars.

Secondary objectives:

To compare the effectiveness of three interventions: photobiomodulation combined with self-cure resin, self-cure resin alone, and photobiomodulation combined with bulkfill photopolymerizable resin in controlling hypersensitivity over time.To assess the clinical performance of the self-cure composite resin in terms of restoration longevity.

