### Clinical protocol

#### Group 1 – photobiomodulation + restoration with self-cure composite resin.

Initial periapical radiograph;Hypersensitivity reading (Wong-Baker Faces Pain Rating Scale for subjective pain of volunteer and SCASS for examiner’s assessment);Application of photobiomodulation;Relative isolation (lip bumper, cotton roll and aspirator);Selective removal of carious tissue with excavator, which involves complete removal of carious dentin from the surrounding walls followed by partial removal of softened dentin from the pulp wall (only Code 6 of MIH-SSS criteria);Cleaning with cotton and water;Application of primer (Stela; SDI, Melbourne, Vic, Australia) on dentin and/or enamel, wait 5 seconds;Application of mild compressed air on adhesive for 3 seconds;Restoration with self-cure composite resin (Stela; SDI, Melbourne, Vic, Australia) extending to adjacent demarcated opacities;Clinical follow up after 48 hours and at four-month intervals for a period of 12 months (modified USPHS index);Hypersensitivity reading after 48 hours and at four-month intervals for a period of 12 months (Wong-Baker Faces Pain Rating Scale for subjective pain of volunteer and SCASS for examiner’s assessment).

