#### Group 3 – photobiomodulation + restoration with bulk-fill composite resin.

Initial periapical radiograph;Hypersensitivity reading (Wong-Baker Faces Pain Rating Scale for subjective pain of volunteer and SCASS for examiner’s assessment;Relative isolation (lip bumper, cotton roll and aspirator);Application of photobiomodulation;Selective removal of carious tissue with excavator, which involves complete removal of carious dentin from the surrounding walls followed by partial removal of softened dentin from the pulp wall (only Code 6 of MIH-SSS criteria);Selective etching of enamel adjacent to demarcated opacities with 35% phosphoric acid (Ultra Etch; Ultradent, Indaiatuba, SP, Brazil) for 20 seconds;Active application of universal adhesive (Ambar; FGM, Joinville, SC, Brazil) on dentin and enamel for 20 seconds (repeat procedure);Application of mild compressed air on adhesive for 5 seconds;Photoactivation for 10 seconds, peak of 1200 Mw/cm^2^ (Radii Cal; SDI, Melbourne, Vic, Australia);Restoration with Tetric N Ceram bulk-fill composite resin (Tetric N Ceram Bulk Fill; Ivoclar Vivadent, Barueri, SP, Brazil) with increments up to 4 mm, extending to demarcated opacities;Photoactivation for 20 seconds (Radii Cal; SDI, Melbourne, Vic, Australia);Clinical follow up after 48 hours and at four-month intervals for a period of 12 months (modified USPHS index);Hypersensitivity reading after 48 hours and at four-month intervals for a period of 12 months (Wong-Baker Faces Pain Rating Scale for subjective pain of volunteer and SCASS for examiner’s assessment).

The interventions will begin without an initial application of local anesthesia. The children will be informed that anesthesia is available and can be administered at any time during the procedure, if necessary.

A children’s toothpaste with 1100 ppm fluoride, which does not contain any components specifically designed for treating dentin hypersensitivity, will be provided to all participants. This toothpaste will be used for daily oral hygiene during the study to ensure consistency across all participants and avoid any confounding factors related to hypersensitivity treatment.

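### A C score on enamel beside a sound restoration ends observation of the tooth, so its later retention and caries are lost and the composite cannot separate material failure from enamel events

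*Protocol article*

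**What the plan says.** The secondary objective in the Objectives section is "To assess the clinical performance of the self-cure composite resin in terms of restoration longevity".

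The Clinical assessment section names three criteria: "retention of the restorative material in the cavity, posteruptive breakdown of the enamel adjacent to the restoration and the occurrence of secondary caries". They are scored with the modified USPHS index by a blinded examiner. The rule for a bad score follows: "The restoration will be characterized as a failure and the tooth will be excluded from the study if the C score is determined", and it applies to any one of the USPHS criteria. Scoring is planned at 48 hours and at 4, 8 and 12 months.

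On the natural reading, a C for adjacent enamel does two things: it makes the restoration a failure and it removes the tooth from the study. The article does not define which degree of enamel breakdown scores C; it relies on a cited source for that.

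**The concern.** Enamel next to a restoration can break down while the restoration stays in place without caries. The Introduction gives a reason to expect this in these teeth: "Darker opacities exhibit a higher susceptibility to fractures due to a greater compromise in their mineral composition". All enrolled molars have MIH-SSS code 5 or 6.

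The rule joins two decisions that need not go together. Calling the event a failure is a matter of endpoint definition. Ending observation is a matter of data collection, and it cannot be undone at analysis. A table of failures by first criterion can still be made from the recorded scores, whatever the analysis plan says. The retention and caries scores from the visits after exclusion cannot, because they were never taken. The longevity objective is about the material, and for these teeth the material's later course is unknown.

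Taken literally, exclusion from the study would also end the tooth's remaining hypersensitivity readings.

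**Working it through.** The documents give no failure rate and no sample size for longevity, so there is no plan figure to reproduce. The stated 66 participants, raised to 75, belong to the hypersensitivity analysis. Only the 25 teeth per arm are taken from the plan; all rates below are assumptions.

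**Step 1. What is lost.** Visits are at 48 hours and 4, 8 and 12 months. An enamel C at month 4 loses two USPHS visits (8 and 12 months); at month 8 it loses one; at month 12 it loses none.

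Let *r* be the 12-month risk of failure by retention or secondary caries, and *e* the risk of an enamel C, independent of *r* within an arm. Restorations that would be sound at 12 months but have an enamel C number 25 × (1 − *r*) × *e*. This is an upper bound on those unobserved at month 12, since an enamel C first seen at month 12 loses nothing.

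- Group 1, *r* = 10%: 25 × 0.90 = 22.5 sound. With *e* = 10%, 20%, 30%: 2.25, 4.5, 6.75.
- Group 3, *r* = 40%: 25 × 0.60 = 15 sound. With *e* = 10%, 20%, 30%: 1.5, 3.0, 4.5.

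This loss occurs whether or not enamel breakdown depends on the resin.

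**Step 2. What the composite shows.** Composite failure = 1 − (1 − *r*)(1 − *e*). The contrast is Group 1 v Group 3, 25 v 25, because both receive photobiomodulation and differ in the resin with its bonding steps. Power is for the two-sided Fisher exact test at 0.05, by exact enumeration. The test is chosen for illustration and is not in the plan.

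| Enamel C, Group 1 / Group 3 | Composite, Group 1 v Group 3 | Difference (points) | Ratio | Power |
|---|---|---|---|---|
| none | 10% v 40% | 30 | 4.0 | 59% |
| 10% / 10% | 19% v 46% | 27 | 2.4 | 42% |
| 20% / 20% | 28% v 52% | 24 | 1.9 | 33% |
| 30% / 30% | 37% v 58% | 21 | 1.6 | 26% |
| 10% / 30% | 19% v 58% | 39 | 3.1 | 77% |
| 30% / 10% | 37% v 46% | 9 | 1.2 | 7% |

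Example, row 2: 1 − 0.90 × 0.90 = 0.19 and 1 − 0.60 × 0.90 = 0.46.

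**Step 3. A smaller contrast.** With *r* of 10% v 30%, the 20-point difference becomes 18, 16 and 14 points at equal enamel rates of 10%, 20% and 30%. With enamel rates of 10% / 20% it is 44 − 19 = 25 points; with 20% / 10% it is 37 − 28 = 9 points.

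Equal enamel rates shrink the difference. Unequal rates can move it either way. The composite by itself does not show which case applies.

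**The case against.** The strongest reply is that adjacent enamel is not foreign to the restoration. The Introduction names poor adhesion to hypomineralized enamel as a main factor in restorative failure, and claims lower contraction stress and a gap-free interface for the self-cure resin. Both resins are placed up to the opacities ("extending to adjacent demarcated opacities" in Group 1, "with increments up to 4 mm, extending to demarcated opacities" in Group 3), so the enamel in question lies at the margin. Group 3 has selective etching and a universal adhesive, while Group 1 has a primer without etching. A difference between resins in marginal enamel breakdown is therefore plausible, and any unacceptable score is a coherent definition of clinical failure.

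This stands, and it rules out two stronger readings. A reader might infer that the rule dilutes a true resin difference. That requires equal enamel rates under both resins, which the documents do not state and their account of adhesion makes uncertain. A reader might also infer that enamel breakdown should be taken out of the failure definition. The documents do not support that: it would call a restoration with broken-down margins a success, and it is a debatable choice of endpoint.

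Pooling Groups 1 and 2 (50 v 25) would give a more striking illustration, with power of 81% before any enamel event. It would also mix the resin with photobiomodulation, which Group 2 does not receive.

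It can also be said that ending observation is a problem for every C score, not only for enamel. That is true of the clause, but the case differs. After loss of the restoration there is no retention left to observe. After an enamel C the restoration may be intact, with its longevity still open.

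**Conclusion.** The point holds as a problem of data collection and reporting for a secondary objective. The clause stops observation of restorations that may be retained and caries-free, and the any-C composite alone does not separate material failure from enamel events. Under the assumed rates, up to about 2 to 7 restorations in Group 1 and 2 to 5 in Group 3 that would be sound at 12 months would not be seen then.

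The direction of any effect on the resin comparison is unknown. Nor is longevity measured by enamel events alone, as a reader might conclude, since retention and secondary caries are in the composite too. The conclusion rests on the natural reading that adjacent enamel breakdown is scored on the modified USPHS index and can reach C. The degree of damage that scores C is not given in the article.

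**What to change.** In the Clinical assessment section:

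- Keep a C score on any criterion as the composite definition of restoration failure.
- Replace the clause that excludes the tooth, so that a C on adjacent enamel does not end scheduled USPHS data collection while the restoration remains in place.
- Record the date and the criterion of each C score.
- Report retention, adjacent enamel breakdown and secondary caries separately by arm, beside the composite.

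This concerns data collection only and leaves the decision on re-treating a tooth untouched. Scores taken after any re-treatment must be flagged, so that they are not read as the course of the first restoration.

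The cost is a little more follow-up data and one extra table, with the examiner, index and visits already planned. The change has to be made before teeth are dropped, because missed visits cannot be reconstructed.

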The preferred approach for teeth with MIH and post-eruptive fractures is restorative treatment with or without absolute isolation. Relative isolation has been shown to be effective in MIH teeth restored with hybrid glass materials [10]. Moreover, some studies have not observed significant differences in the longevity of resin restorations when comparing relative and absolute isolation methods [10–13].

Stela composite resin (Southern Dental Industries) is an innovative, high-performance, self-cure composite with a catalyst that initiates the curing process at the restoration interface. The polymerization sequence attenuates contraction tension by enabling an interface with no gaps, reducing postoperative sensitivity and the risk of premature failure [14–19]. This product has a simple process and fast execution, which is particularly beneficial for children with MIH. There is a need for the investigation of procedures aimed at reducing hypersensitivity and materials that can enhance the longevity of restorations, especially on teeth affected by MIH to improve clinical outcomes, minimize the need for additional interventions and enhance the quality of life of patients.

Therefore, the aim of the proposed study is to determine whether photobiomodulation combined with a new photopolymerizable resin improves hypersensitivity in MIH-affected carious molars. The secondary objectives are to evaluate the effectiveness in controlling hypersensitivity over time and to assess the clinical performance of the self-cure composite resin in terms of restoration longevity.

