### Ethical aspects

The study will be conducted in accordance with the ethical precepts stipulated in the Declaration of Helsinki (World Medical Association, 2008) and the norms governing research involving human beings stipulated in Resolutions nº 466/12 and 510/2016 of the National Board of Health. The study received approval from the Human Research Ethics Committee of Nove de Julho University (certificate number: 83027624.2.0000.5511/approval date: December 4, 2024) and was registered in ClinicalTrials.gov (NCT06538142, Last Update: January 17, 2025). The legal guardians will agree to the children’s participation by signing a statement of informed consent. Recruitment will begin after approval from the Human Research Ethics Committee. The participants will be informed that they can withdraw from the study at any time for any reason, if they so desire. The researchers may withdraw participants from the study if it is considered necessary.

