### Statistical analysis

The data will be presented using descriptive statistics. Continuous variables will be described with mean and standard deviation, and categorical variables by relative frequency. Statistical analyses will be conducted using SPSS software (version 28.0, IBM, USA). For comparisons of the Wong-Baker Faces Pain Rating Scale and SCASS scales, a repeated measures analysis of variance (ANOVA) will be used, considering the three groups and five time points of the study. This analysis will address the objective of comparing the effectiveness of interventions in controlling hypersensitivity over time. Post-hoc comparisons will be made using the Bonferroni adjustment to control for Type I error in multiple comparisons. The normality of the data distribution and the homogeneity of variance will be confirmed by the Shapiro-Wilk and Levene tests, respectively. The presence of sphericity will be verified using the Mauchly test, and if violated, corrections such as Greenhouse-Geisser will be applied. For secondary outcomes, repeated measures ANOVA will also be used to compare differences over time among the three intervention groups. Post-hoc analyses with Bonferroni correction will be applied when necessary. Effect sizes (partial eta squared) will be reported to assess the magnitude of differences between interventions. Additionally, Pearson or Spearman correlation coefficients will be used to explore associations between changes in hypersensitivity and secondary outcomes, depending on data distribution. Sensitivity analyses using an intention-to-treat approach may also be performed to assess the robustness of the findings. A significance level of 0.05 will be adopted for all analyses.

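### Teeth whose restoration fails leave the study and intention-to-treat is only optional, so the later hypersensitivity comparison is between non-failed teeth and can be biased, mainly in contrasts with Group 3

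*Protocol article*

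**What the plan says.** - **Exclusion rule** (Clinical assessment): a C score makes the restoration a failure, and "the tooth will be excluded from the study if the C score is determined for any of the USPHS criteria". The criteria arise after treatment: "The criteria will be the retention of the restorative material in the cavity, posteruptive breakdown of the enamel adjacent to the restoration", and secondary caries. The examiner who scores them is blinded.
- **Unit** (Description of sample): one molar per child, so excluding the tooth removes the participant.
- **Hypersensitivity analysis** (Statistical analysis): for Wong-Baker and SCASS, "a repeated measures analysis of variance (ANOVA) will be used, considering the three groups and five time points of the study". The time points are baseline, 48 hours, and 4, 8 and 12 months.
- **Analysis set** (Statistical analysis): the only mention of intention-to-treat is "Sensitivity analyses using an intention-to-treat approach may also be performed to assess the robustness of the findings".
- **Longevity** (Objectives): a secondary aim is "To assess the clinical performance of the self-cure composite resin in terms of restoration longevity".
- **Rationale** (Introduction): failure and re-treatment are described as more frequent in MIH teeth, without a rate. The self-cure material is credited with "reducing postoperative sensitivity and the risk of premature failure".
- **Sample size**: 66 children, raised to 75 for dropouts. Exclusions for failure are not mentioned there.

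**The concern.** Randomisation makes the three groups comparable at the start. They stay comparable only if what happens after treatment does not decide who is analysed. Here a treatment outcome, failure of the restoration, does decide it.

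Two conditions turn such a rule into bias between arms: failure must differ by arm, and failure must be related to sensitivity. The protocol's own rationale makes both plausible, since it expects the self-cure resin to lower both sensitivity and failure. Groups 1 and 2 receive that resin and Group 3 receives the bulk-fill resin. If one material fails more often and its failed teeth are the more sensitive ones, that arm loses its worst readings and its remaining teeth look better than the arm as randomised. On the protocol's expectation this would flatter Group 3 and count against the self-cure resin.

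The analysis method adds to the loss. Repeated measures ANOVA in its classical form needs all five readings. A tooth excluded at 4 or 8 months then drops out entirely, including its valid baseline and 48-hour readings.

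**Working it through.** **1. The plan's own figure.** Inputs from Sample size calculation: f = 0.352, alpha 0.05, power 80%, k = 3 groups, m = 5 measures. For the between-groups test, lambda = f² × N × m / (1 + (m − 1) × rho), with k − 1 and N − k degrees of freedom. The article does not give rho. With rho = 0.75 (assumed), N = 66 gives lambda = 0.1239 × 66 × 5 / 4 = 10.22 and power 0.805, which reproduces the stated 66. With rho = 0.5 the same test would need only 51.

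**2. Room for losses.** 75 − 66 = 9 children, and 9/75 = 12%. Dropouts and failure exclusions both draw on these 9.

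| Analysed N | Loss from 75 | Power, rho 0.75 | Power, rho 0.5 |
|---|---|---|---|
| 75 | 0% | 0.857 | 0.942 |
| 66 | 12% | 0.805 | 0.908 |
| 64 | 15% | 0.791 | 0.898 |
| 60 | 20% | 0.761 | 0.876 |
| 52 | 30% | 0.692 | 0.819 |

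The loss rates are assumptions. The article gives no failure rate.

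**3. Bias if failed teeth are removed.** Assume no true difference between arms. Let standardised 12-month sensitivity have correlation c with a latent tendency to fail, and let a fraction p fail. The mean among retained teeth is −c × phi(z) / (1 − p), where z is the upper-p normal quantile.

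- p = 0.10: phi(1.282) / 0.90 = 0.1755 / 0.90 = 0.195
- p = 0.30: phi(0.524) / 0.70 = 0.3477 / 0.70 = 0.497

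With failure of 10% in Groups 1 and 2 and 30% in Group 3, the spurious Group 1 minus Group 3 difference is c × (0.497 − 0.195) = c × 0.302:

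- c = 0: 0
- c = 0.3: 0.09 SD
- c = 0.5: 0.15 SD

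Simulation gives the same values (0.089 and 0.149). With 10% failure in every arm the difference is about 0 at each c tried (0, 0.3 and 0.5).

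**4. False-positive rate.** In 4,000 simulated trials of 25 per arm, with the same 10/10/30% failure and a one-way test at the 0.05 level, the type I error was 0.049 at c = 0, 0.059 at 0.3, 0.068 at 0.5 and 0.101 at 0.7. The inflation is modest unless failure and sensitivity are closely linked.

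**The case against.** **An unseen analysis plan may settle this.** It could define analysis sets, but the exclusion and the optional status of intention-to-treat are already stated here. No analysis plan can recover readings that were never taken.

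**The bias may be small or absent.** This stands. The documents give neither failure rates by arm nor the link between failure and sensitivity. Groups 1 and 2 receive the same resin, so the resin mechanism gives no reason for different failure between them. The C score is assigned by a blinded examiner, so the exclusion is not steered by knowledge of allocation. However, once failed teeth are no longer measured, the trial cannot show that the bias was small.

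Four stronger readings are tempting and not supported:

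- *That the exclusion itself biases longevity.* The restoration is classed as a failure as well as being excluded, so the event can be counted. Ending follow-up at failure is acceptable in a time-to-failure or failure-proportion analysis. The Statistical analysis section names another method ("For secondary outcomes, repeated measures ANOVA will also be used to compare differences over time among the three intervention groups"), but the suitability of that method is a separate question.
- *That the operator can remove children knowing their allocation.* Ethical aspects says "The researchers may withdraw participants from the study if it is considered necessary". This is a general clause, and nothing in it assigns the decision to the operator.
- *That power falls from 80% to 68%.* With 15% dropout and an assumed 20% failure, 75 × 0.85 × 0.80 = 51, and power is 0.68 at rho 0.75 but 0.81 at rho 0.5. Dropout alone already gives about 0.79 at rho 0.75. The failure rate and rho are both assumed.
- *That exclusion would erase a true effect.* Taking mean SCASS as 0.5 in intact and 1.8 in failed teeth, with 10% versus 30% failure, 0.89 − 0.63 = 0.26 becomes 0 after exclusion. This follows by construction, because the whole effect is assumed to run through failure. None of these inputs is in the article.

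**Conclusion.** The defect in the wording is certain: a post-randomisation outcome removes participants, and no all-randomised analysis is committed to. As written, the hypersensitivity comparison at 4, 8 and 12 months is between non-failed teeth.

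The consequence is a possible bias of unknown size, chiefly in contrasts with Group 3. It is near zero if failure is equal across arms or unrelated to sensitivity, and about 0.09 to 0.15 SD under the assumed 10% versus 30% failure and correlation of 0.3 to 0.5. These figures are illustrations, not estimates for this trial. The limit of 9 losses rests only on the stated 75 and 66, while the power at each loss depends on the unstated correlation. The point does not extend to bias in longevity or to operator discretion. It should still be corrected, because readings not taken cannot be restored later.

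**What to change.** 1. In Clinical assessment, delete the exclusion clause. Record a C score as a failure event for the longevity objective.
2. Continue Wong-Baker and SCASS readings at the remaining scheduled visits after a failure, and record any re-treatment and its date. What care a failed tooth receives is a clinical matter outside this point.
3. In Statistical analysis, make the primary analysis include all randomised children as allocated, with a method that keeps incomplete series, for example a mixed model for repeated measures. Relabelling intention-to-treat as primary within classical repeated measures ANOVA would not suffice, because that method still drops incomplete series.
4. Make the intact-restorations-only analysis the sensitivity analysis.

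**Cost.** The wording of two sections changes, and failed teeth must be seen at recalls that are already planned. Readings after re-treatment will partly reflect that re-treatment. The intact-only analysis and the recorded dates let the reader judge how much this matters.
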